#### Modified follow-up by partial exclusion

Patients are recruited before fracture reduction because immobilization takes place immediately after reduction. A part of included patients will receive surgical fixation in the first treatment week, due to unsuccessful fracture reduction. Consequently, it is unavoidable to include patients who will eventually be unsuitable to answer the primary research question. Patients receiving surgical fixation before the first follow-up appointment (T1) will not be encountered in the needed patient numbers. Recovery of these patients will be evaluated by questionnaires only (Fig. 3).

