**Methods/design:**

This multicenter cluster randomized controlled trial will compare initial immobilization with a circumferential below-elbow cast versus a below-elbow plaster splint in reduced DRFs. Randomization will take place on hospital-level (cluster, *n* = 10) with a cross-over point halfway the inclusion of the needed number of patients per hospital. Inclusion criteria comprise adult patients (≥ 18 years) with a primary displaced DRF which is treated conservatively after closed reduction. Multiple trauma patients (Injury Severity Score ≥ 16), concomitant ulnar fractures (except styloid process fractures) and patients with concomitant injury on the ipsilateral arm or inability to complete study forms will be excluded. Primary study outcome is fracture redisplacement of the initial reduced DRF. Secondary outcomes are patient-reported outcomes assessed with the Disability Arm Shoulder Hand score (DASH) and Patient-Rated Wrist Evaluation score (PRWE), comfort of the cast, quality of life assessed with the EQ-5D-5L questionnaire, analgesics use, cost-effectiveness and (serious) adverse events occurence. In total, 560 patients will be included and followed for 1 year. The estimated time required for inclusion will be 18 months.

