### Data analysis

General descriptive statistics will be performed on baseline patient and fracture characteristics. Patients will be analyzed according to the intention-to-treat principle.

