## Discussion

This study is an open-label trial. Allocated treatments are visually different for the treating physician and the patient. Randomization status will therefore not be blinded.

Heterogeneity of the study population concerning fracture characteristics and age could be pointed out as a limitation. However, this pragmatic study tries to represent the actual patient population.

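### Patients operated on before T1 get no primary outcome although intention to treat is stated without exception, and the rule turns on receipt of surgery rather than on the post-reduction radiograph

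*Protocol article*

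**What the plan says.** The section on modified follow-up explains the order of events: "Patients are recruited before fracture reduction because immobilization takes place immediately after reduction". It expects that "A part of included patients will receive surgical fixation in the first treatment week, due to unsuccessful fracture reduction", and concludes that "it is unavoidable to include patients who will eventually be unsuitable to answer the primary research question". The operative rule is "Patients receiving surgical fixation before the first follow-up appointment (T1) will not be encountered in the needed patient numbers", where the verb evidently means counted. It adds that "Recovery of these patients will be evaluated by questionnaires only".

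The Data analysis section states: "Patients will be analyzed according to the intention-to-treat principle". It makes no exception for the patients just described.

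The abstract describes the included patients as having "a primary displaced DRF which is treated conservatively after closed reduction". The inclusion list in the body asks only for age and a fracture that requires closed reduction. The Discussion says of this open-label trial: "Randomization status will therefore not be blinded".

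The primary outcome is redisplacement of the initially reduced fracture, read on radiographs at 1, 2 and 5 weeks against the Dutch guideline limits. Table 1 schedules films at T0 (before and after reduction) and at T1 to T3.

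**The concern.** Patients are enrolled and immobilised under a hospital allocation that everyone can see. Whether someone is operated on before T1 is therefore settled after allocation, by clinicians who know the cast type. Questionnaire-only follow-up leaves these patients without T1 to T3 study films, so in practice they cannot enter the primary analysis. That does not sit with an unqualified intention-to-treat statement.

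The stated reason and the trigger also select different patients. The reason is a reduction that failed. The trigger is an operation before a given visit. The mismatch works in two ways:

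- A fracture that was well reduced, slipped and was fixed before T1 is a true primary event, and the rule removes it.
- A fracture that was never acceptably reduced but was not operated on before T1 stays in. It may already exceed the limits at T1 and be scored as redisplacement.

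The Background says that redisplaced fractures are nowadays generally treated surgically, so outcome and trigger are linked on the protocol's own account. If early slips or early operations differ by cast type, the primary comparison can shift in either direction.

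**Working it through.** **1. The passages side by side**

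| Question | Modified follow-up section | Elsewhere in the article |
|---|---|---|
| When does the patient enter? | Before reduction; cast follows at once | Consent before the study procedure (Participants and recruitment) |
| Why are patients set aside? | Unsuccessful reduction | Fig. 3 legend lists the alignment limits and casting at least until the first control radiographs |
| What sets them aside? | Any surgical fixation before T1 | – |
| What data remain? | Questionnaires only | Primary outcome needs films at 1, 2 and 5 weeks |
| Who is analysed? | Not stated as an analysis set | Intention to treat, no exception |

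For the primary outcome, the second and last columns cannot both be followed as they stand.

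**2. The plan's own figures**

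The needed number is 500 analysable patients. With 10% loss, 500 / 0.9 = 556, which agrees with the stated 560.

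Baseline power for the illustration uses a two-sided pooled two-proportion test at 0.05 with n = 250 per arm, 20% against 10%:

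- SE under the null = √(2 × 0.15 × 0.85 / 250) = 0.0319
- SE under the alternative = √((0.16 + 0.09) / 250) = 0.0316
- Power = Φ((0.10 − 1.96 × 0.0319) / 0.0316) = Φ(1.18) = 0.88

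A simulated random-intercept logistic model (10 hospitals, 25 + 25 patients, intra-class correlation 0.06, 2,000 runs) also gives 0.88 two-sided. The stated 93% is matched only one-sided (0.933). That is a separate matter; 88% is the reference here.

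**3. What removal would do (assumed shares)**

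The article gives no early-surgery share and no split by arm. Let p be the true redisplacement rate and e the share of an arm that redisplaces and is operated on before T1. The analysed rate is (p − e) / (1 − e). I keep 250 analysed per arm, because removed patients do not count towards the needed number.

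True rates 20% splint, 10% cast:

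| Removed, splint / cast | Analysed rates | Difference | Power |
|---|---|---|---|
| 0% / 0% | 20.0% / 10.0% | 10.0 points | 88% |
| 2% / 1% | 0.18/0.98 = 18.4% / 0.09/0.99 = 9.1% | 9.3 points | 86% |
| 5% / 2% | 0.15/0.95 = 15.8% / 0.08/0.98 = 8.2% | 7.6 points | 75% |
| 2% / 5% | 0.18/0.98 = 18.4% / 0.05/0.95 = 5.3% | 13.1 points | inflated |

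True rates 20% in both arms: removing 5% from each leaves the rejection rate at 0.05. Removing 5% from splint and 2% from cast gives 15.8% against 18.4%, and the rejection rate rises to about 0.12.

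**4. How demanding the assumptions are**

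In the 2% / 1% row, a tenth of all redisplacements in each arm (2/20 and 1/10) are found and fixed before T1. In the 5% / 2% row it is a quarter in the splint arm (5/20) and a fifth in the cast arm (2/10).

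**The case against.** The strongest reply is that the rule mainly catches what it says it catches. No film is scheduled between the post-reduction film and T1, so surgery before T1 would ordinarily be decided on the T0 film. A well-reduced fracture is lost only if it slips, is seen on an unscheduled film and is operated on, all within about a week. The Fig. 3 legend points the same way: it lists the alignment limits and refers to casting at least until the first control radiographs, so the flowchart may already sort patients on alignment. This stands as a reason to expect few lost events. It cannot be confirmed, because the figure is not available here, and the rule in the text still covers any surgery before T1.

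Second, the section speaks of needed numbers and follow-up, and does not literally define an analysis set. A fracture that was never reduced cannot redisplace, so some restriction to reduced fractures fits the objective. The abstract's reference to conservative treatment can be read as describing that same target population. This also stands. Equal removal of genuine reduction failures unrelated to the cast would change the population without biasing the comparison. It does not explain why the restriction rests on surgery and not on the film, nor does it square questionnaire-only follow-up with unqualified intention to treat.

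A reader might go further and infer that these patients vanish from the trial, or that the comparison is known to be biased with a serious loss of power. The documents support neither. The patients stay in questionnaire follow-up, and conversion to surgery is a secondary outcome from which no passage excludes early cases. Because each hospital uses both casts, stable differences between hospitals in the threshold for surgery affect both arms. A threshold that differs by cast type is possible but not documented.

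**Conclusion.** The point holds as an internal inconsistency with a badly placed trigger. It should be fixed, with medium confidence. The modified follow-up section leaves patients operated on before T1 without a primary outcome, the Data analysis section promises intention to treat without exception, and the dividing line is an unblinded decision after allocation.

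The size of any bias is unknown. It depends on how many well-reduced fractures are fixed before T1 and on whether that number differs by arm, and the article gives neither. The drop from 88% to 86% or 75% and the rejection rate of about 0.12 are illustrations in which every removed patient is an early redisplacement. They are not estimates for this trial. The direction is likewise open.

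**What to change.** Reconcile the modified follow-up section, the Fig. 3 legend and the Data analysis section as follows:

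1. Define the primary analysis set by the T0 post-reduction radiograph: alignment within the limits the protocol already states, whatever surgery follows. If possible, have the film read without knowledge of cast type.
2. Within that set, count surgical fixation for loss of alignment before T1 as redisplacement, and record the reason for each early operation.
3. Call this set modified intention-to-treat.
4. Report surgery before T1 by arm.
5. Add a sensitivity analysis of all allocated patients, labelled as a composite of failed reduction or redisplacement. The label matters because a failed reduction is not a redisplacement under the primary outcome definition.

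The cost is wording and analysis. The T0 post-reduction films are already taken, and no clinical decision changes. Some patients who would have been replaced now count, and others with unacceptable T0 alignment leave the primary set.

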**Fig. 3 Fig3:**
[figure not shown]
CAST study follow-up flowchart. ^*^Type of treatment depends on randomization status of the hospital. ^*μ*^ Unacceptable alignment conform the Dutch guideline: > 15° of dorsal angulation, > 20° of volar angulation, < 15° of radial inclination, > 3 mm of radial shortening and > 2 mm intra-articular step-off or gap. ^∆^ Cast immobilization, at least until the first control radiographs are taken. ^£^ All measurements encountered in Table 1. ^¥^ All questionnaires encountered in Table 1

#### (serious) adverse events reporting

All adverse events reported by the patient or observed by the treating physician or researcher will be recorded. Serious adverse events (SAE) will be reported through the web portal *ToetsingOnline* of the Central Committee on Research Involving Human Research (Dutch CCMO) to the Medical Research Ethics Committee of Erasmus Medical Center in Rotterdam, which approved the protocol. SAE reporting will take place within 7 days after the sponsor has first knowledge of a serious adverse event resulting in death or is life-threatening. All other SAE will be reported within 15 days.

Adverse events are defined as:
Cast or splint related problemsFracture redisplacement treated with surgical reduction and fixationComplex regional pain syndrome (CRPS) defined conform the Budapest criteriaDisabling fracture mal-union or non-union

Study related serious adverse events are defined as:
Compartment syndrome

#### Sample size

The sample size calculation is based on the results of our recent retrospective study [14]. We hypothesize that fracture redisplacement occurs in 10% of circumferential casted patients versus 20% in splinted patients. A total of 500 patients is needed to detect superiority of a circumferential cast. The sample size calculation is based on a mixed-effects logistic regression, to account for clustering using a random intercept for the hospitals. The intra-class correlation coefficient between the different hospitals for the proportion of fracture redisplacement is assumed to be 0.06, which is generally reported in the literature for hospital processes. From the expected proportions of redisplacement in the two groups, we calculated the hospital-specific log odds of secondary displacement in the circular cast group, equal to − 2.275 and log odds ratio of redisplacement between the two groups equal to 0.84. This calculation is based on the formula that links the cluster-specific coefficients in the mixed-effects logistic regression with the population coefficients averaged over the hospitals. With a power of 93%, 50 patients per hospital need to be included, resulting in a total number needed of 500 (10 participating hospitals). Additionally, we also calculated the needed number of patients using a two-sample test for proportions. Using the same assumptions, namely difference between groups, a significance level of 0.05 and a power of 90%. This resulted in 490 needed patients in total. Accounting for a 10% loss to follow-up, a total of 560 (280 patients per group) are required.

To improve awareness of the study in all participating centers and thereby advert for reaching targeted sample size, a local investigator is appointed in each hospital. This local investigator is a physician who supervises the study. This person is easily accessible and will promote the study on a regular base. We send a newsletter every 2 months to inform about the study progression.

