## Background

Displaced distal radius fractures (DRF’s) are very common in the adult population and their incidence is still increasing because of the ageing population [1, 2]. In the Netherlands, the incidence of DRFs is estimated at 20 per 10.000 persons per year [3]. Two-thirds of DRFs in adults are displaced and require closed reduction [4]. After successful reduction, DRFs are generally immobilized using a non-circular splint or a circumferential cast. Unfortunately, a large number of reduced DRF’s (32–64%) redisplace during cast immobilization in the first treatment weeks [5–7]. Whereas redisplacement of DRFs was previously accepted or reduced in a second attempt, nowadays these redisplaced fractures are generally treated surgically [8, 9].

Although surgical reduction and fixation generally results in a satisfying outcome, preventing fracture redisplacement and thereby preventing surgery would be the preferred scenario. Therefore, it is important to discover factors that could predict or prevent fracture redisplacement. Studies focusing on this topic are mostly assessing non-modifiable factors predicting fracture redisplacement [5–7, 10]. Known factors enhancing the risk on fracture displacement are female gender, age > 60 years and fractures with dorsal comminution [10]. However, it is unknown if type of cast immobilization is of influence.

Existing literature concerning the role of cast immobilization on fracture re-displacement is scarce and inconclusive [11]. Recently, Caruso et al. (2019) performed a randomized controlled trial comparing the effect of above-elbow casting and below-elbow casting on maintaining reduction and found similar results in both groups [12]. Patient-reported outcome after 1-year follow-up did not differ amongst both treatment groups. A randomized controlled trial by Wik et al. (2009) evaluated fracture alignment during 5 weeks follow-up in 72 patients with displaced DRF’s treated with dorsal splinting versus circumferential casting [13]. The circumferential casting group showed a significantly better result for radial length at 5 weeks but no difference concerning dorsal angulation. Recently, our research group conducted a retrospective study in 500 patients with reduced DRFs and found significantly less fracture redisplacement in fractures treated with circumferential casting compared with splinting, namely 17% versus 29% [14].

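### The two sample-size results (93% power at 500 patients; 490 patients for 90% power) cannot both follow from the stated assumptions, and the sidedness of the 0.05 level is not stated

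*Protocol article*

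**What the plan says.** All the figures are in the protocol article, Sample size section. The planning hypothesis is: "We hypothesize that fracture redisplacement occurs in 10% of circumferential casted patients versus 20% in splinted patients". The aim is put as "A total of 500 patients is needed to detect superiority of a circumferential cast". The main calculation uses a mixed-effects logistic regression with a random hospital intercept, an ICC of 0.06, hospital-specific log odds of −2.275 in the circumferential cast group and a log odds ratio of 0.84. Its result is: "With a power of 93%, 50 patients per hospital need to be included, resulting in a total number needed of 500 (10 participating hospitals").

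A second calculation follows: "we also calculated the needed number of patients using a two-sample test for proportions". It is said to share the assumptions of the first, "namely difference between groups, a significance level of 0.05 and a power of 90"%, and its result is: "This resulted in 490 needed patients in total". A 10% allowance for loss to follow-up leads to 560.

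Neither calculation says whether 0.05 is one-sided or two-sided.

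**The concern.** The cross-check names its method and nearly all its inputs, so a reader can repeat it, and 490 does not come out. The 93% also looks high, because a simple two-sided test with 500 patients stays below 90% for these rates.

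These figures are the published justification for the trial's size. As printed, the simple calculation (490) appears to confirm the model-based one (500) with a little to spare. On a two-sided reading it needs more than 500, and the type II error at 500 is about 10% rather than 7%. On a one-sided reading, the protocol is using a one-sided 0.05 test without saying so. That allows twice the directional error of a two-sided 0.05 test.

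**Working it through.** **Inputs** (all from the Sample size section): p1 = 0.10, p2 = 0.20, alpha = 0.05, power 90% for the cross-check, ICC = 0.06, 10 hospitals with 50 patients each. The cross-over halfway (Study design and randomization) puts 25 patients per arm in each hospital. Sidedness is not given, so both readings are run.

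**Step 1: the protocol's coefficients.** These reproduce.
- Hospital variance on the logit scale: 0.06 × (π²/3) / 0.94 = 0.210.
- Factor from population-averaged to hospital-specific coefficients: √(1 + 0.346 × 0.210) = 1.0357.
- Cast group: logit(0.10) × 1.0357 = −2.197 × 1.0357 = −2.276 (printed −2.275).
- Log odds ratio: 0.811 × 1.0357 = 0.840 (printed 0.84).

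The model and the scale of the ICC are therefore not in doubt.

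**Step 2: the cross-check of 490 at 90% power.** For the unpooled formula, n per arm = (z_alpha + z_power)² × [p1(1−p1) + p2(1−p2)] / (p2−p1)².
- Two-sided: (1.960 + 1.2816)² × 0.25 / 0.01 = 10.507 × 25 = 262.7, so 263 per arm and 526 in total.
- One-sided: (1.645 + 1.2816)² × 25 = 8.564 × 25 = 214.1, so 215 per arm and 430 in total.

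| Formula | Total N, two-sided | Total N, one-sided | Power at 490, two-sided | Power at 490, one-sided |
|---|---|---|---|---|
| Pooled | 532 | 434 | 87.5% | 92.9% |
| Unpooled | 526 | 430 | 87.9% | 93.1% |
| Arcsine | 522 | 426 | 88.1% | 93.3% |
| Continuity-corrected | 572 | 474 | not run | not run |

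Formulas on the log odds ratio, a different method from the one named, give 556 or 502 two-sided and 454 or 410 one-sided. None of these is 490. Leaving aside the continuity correction, 490 is too low by 32 to 42 patients on the two-sided reading (32/522 = 6%, 42/532 = 8%) and too high by 56 to 64 on the one-sided reading.

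**Step 3: the 93% at 500.** The protocol's model was simulated with its own coefficients: 10 hospitals, 25 + 25 patients each, random-intercept logistic regression fitted by maximum likelihood, 3,000 runs, Monte Carlo standard error about 0.5 points. Under no effect (1,500 runs) the two-sided rejection rate was 5.1% (Wald) and 5.5% (likelihood ratio), so the test is roughly at its nominal level.

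| Method at 500 patients | Two-sided 0.05 | One-sided 0.05 |
|---|---|---|
| Two proportions, pooled | 88.2% | 93.3% |
| Two proportions, unpooled | 88.5% | 93.5% |
| Two proportions, arcsine | 88.7% | 93.7% |
| Random-intercept model, Wald | 89.7% | 94.6% |
| Random-intercept model, likelihood ratio | 90.2% | not run |

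Two-sided, the printed 93% is about 3 points too high, well beyond simulation error. One-sided, it is attainable.

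**Step 4: both figures together.** A two-sided level gives neither 93% at 500 nor 490 at 90%. A one-sided level supports 93% at 500 but makes the cross-check 426 to 434. No single convention gives both.

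**Step 5: enrolment.** 500 / 0.9 = 556, which fits the rounded 560. The 490 did not set the target. With all 560 evaluable, the two-sided model gives 92.5% to 92.9%.

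**The case against.** The strongest objection concerns the 93%. A reader might infer that the stated assumptions simply give 89% to 90%. The document does not support that: it states no sidedness, it speaks of detecting superiority of one named cast, and a one-sided 0.05 test does give about 93% to 95%. This stands, so the 93% cannot be called wrong outright. Against a one-sided reading, the primary objective is neutral as to which cast is better. That makes the two-sided reading the more natural one but does not settle it.

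The 490 may also have an innocent origin. The two-sided arcsine total multiplied by (1 − ICC) is 522 × 0.94 = 491, and a one-sided test at 93% power needs 484 to 494. The first uses a cross-over factor that the text does not mention; the second contradicts the printed 90%. Either may explain the number, but neither is the calculation described.

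The practical effect is small. Even two-sided, 500 evaluable patients give about 90% power. A reader might infer that the trial is underpowered or should enrol more, or that a null result would be misread. The figures do not support this: the loss is about 3 points, and a null result would be judged from its confidence interval.

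A reader might also take the planning rates as a further error, because the Background reports that the retrospective study found "significantly less fracture redisplacement in fractures treated with circumferential casting compared with splinting, namely 17% versus 29"%. The 10% and 20% are put forward as a hypothesis, and the simple two-sided test at 500 has about 89% power at 17% versus 29% as well. That is a planning choice and not part of this point.

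**Conclusion.** The point holds in this form: the sidedness is missing, the cross-check of 490 is wrong under either convention, and the 93% at 500 holds only for a one-sided 0.05 test. Two-sided, the power at 500 is about 90% in the protocol's own model.

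The cross-check result rests only on the stated rates, level and power. The model result also rests on the protocol's random-intercept structure, with equal arms of 25 per hospital and no hospital-by-period variation. The covariates planned for the primary analysis are not part of the stated calculation and were not modelled.

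This is a modest reporting error. It does not show that the enrolment target of 560 is inadequate.

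**What to change.** State whether the 0.05 level is one-sided or two-sided, and make both calculations follow it.
- If two-sided: restate the power at 500 evaluable patients as about 90%, and replace 490 with 522 to 532 (naming the formula used) or delete the cross-check.
- If one-sided: say so explicitly, keep the 93%, and replace 490 with 426 to 434 or delete the cross-check.
- If 490 came from a cross-over factor or from a different power, state that input instead.

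The cost is a few sentences of text. Enrolment, design and analysis do not change. On the two-sided reading the stated power becomes slightly less favourable.
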